### Expert rating

3.7

To put the NLP model performance into relation to human performance, we will implement an online survey using the SoSci Survey platform for exploratory comparison. Licensed psychotherapists and clinical psychologists will be recruited via email invitations. Each participant will evaluate the well-being and stress levels of 24 anonymized journal entry samples by estimating the three MDBF subscales and the PSS-4 score. The number of items are chosen to keep the completion time around 45 min (approx. 1.5 min per entry). The presentation order will be randomized between participants. Ratings will have to be made on continuous sliders (one-decimal precision), ranging from the minimum to maximum values of the respective questionnaires. This format ensures direct comparability with the model predictions, which also yield decimal outputs. As an incentive, participants will receive feedback at the end of the study: the journal entries will be presented again, along with their corresponding ground truth values, allowing the experts to compare their own assessments to the actual scores.

### Participants’ support and guidance

3.8

Throughout the study period, participants will receive technical and psychological support if needed and the option to ask questions via the messenger service. Any adverse events and negative effects will be systematically recorded. Since the target group partly consists of at-risk participants with elevated psychological burden, close monitoring and accessibility in the event of psychological crises or other incidents are crucial, making intensive support essential. In the event of unexpected incidents that pose an acute risk to participants due to study conditions, the entire study will be immediately terminated. Participants can contact the study team at any time in such cases and opt out of the study at any time.

## Statistics

4

### Sample size calculation

4.1

In this NLP study, classical power analysis is not directly applicable, as the model performance depends on several factors such as training data points, model architecture, and transfer learning effects. Therefore, based on preceding transfer learning literature, 500 data points (D) per group (type and speak) are targeted [60, 61]. Each participant is expected to contribute one data point daily over the study duration of 14 days (d). A dropout rate of 28% (r) is assumed based on comparable studies [62–64]. The number of participants is calculated to be 50 participants per group (100 total):$$N=\frac{D}{d\times (1-r)}=\frac{500}{14\times (1-0.28)}\approx 49.6\approx 50$$

### Statistical analysis

4.2

#### Baseline assessment

4.2.1

Baseline questionnaire data will be summarized descriptively, and Spearman’s rank correlations will examine relationships between DASS-21 subscales, WHO-5, and SCS-K-D scores. Differences by sex and randomized group (type vs. speak) will be explored using two-way ANOVA. *P*-values will be reported for reference, but the study is not powered to detect baseline differences.

Daily measures of mood (MDBF subscales), stress (PSS-4), and state self-control (SSCCS) will be analyzed using linear mixed-effects models with random intercepts for participants to account for repeated measurements. Baseline well-being measures (SCS-K-D, DASS-21, WHO-5) and group assignment will be included as fixed effects to explore whether baseline characteristics predict daily mood and self-control. Daily observations will be included only for days with completed journals; the models naturally handle these unbalanced repeated measures. Additionally, person-level averages of daily mood and state self-control may be correlated with baseline measures using Spearman’s rank correlation as a descriptive check.

#### RQ1: NLP analysis

4.2.2

The spoken journal entries will be transcribed using Whisper [65]. All journal entries will be preprocessed according to standard NLP procedure (tokenization, lowercasing, lemmatization, and stop-word removal) to generate sparse representations [e.g., term frequency–inverse document frequency; TF–IDF). Additionally, dense representations (e.g., contextual embeddings from German pre-trained transformer-based models like GBERT [66] or German-BERT [67]] will be generated. Here, preprocessing will be limited to the model-specific tokenization procedure.

The comparison of architecture classes is itself part of the study, as prior literature has not yet established a best-performing architecture for journaling data. Therefore, different supervised machine learning models will be employed for this regression task, ranging from classical approaches (e.g., random forest regression or support vector regression) to transformer-based deep learning models (e.g., BERT-based regression head). Separate predictive models will be trained on the above-mentioned representations for each outcome variable (MDBF subscales, PSS-4). We will additionally evaluate end-to-end fine-tuning of a smaller transformer model (e.g., a distilled German BERT variant), which will operate directly on tokenized journal entries rather than precomputed representations. Here, we acknowledge the higher risk of overfitting compared to our main representation-based approach.

As a baseline, a mean predictor will be implemented. Model performance will be quantified using root mean squared error (RMSE) and mean absolute error (MAE) to capture prediction error magnitude, and Pearson correlation to assess the strength of association between predicted and observed scores. All models will be evaluated using k-fold cross-validation. To account for repeated measures within participants, cross-validation will be conducted at the participant level, such that all entries from a given participant are assigned exclusively to either the training set or the test set. To examine group differences, models will be trained and evaluated separately for the written and transcribed groups. Predictive performance metrics will then be compared across groups. Differences in performance will be formally tested using bootstrapped confidence intervals to provide robust inference without assuming normality of error distributions.

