Journaling apps are among the most downloaded mental health apps [21, 22]. Features typically include logging of text entries, mood tracking, reflection prompts, and visualization of entries. Some apps incorporate AI features such as chatbots or automated text analysis, but these remain rare and lack scientific validation [23]. To date, few apps have been tested in controlled studies, and evidence on effectiveness and user preferences is scarce [24, 25].

NLP enables automatic assessment of emotions from text. Applications include monitoring depression severity [26], detecting suicidal tendencies [27], and tracking stress [28]. Transformer-based models such as BERT or RoBERTa are state-of-the-art for sentiment analysis and mental health prediction tasks [29–31]. However, research on NLP applied to journaling data is limited. Existing work has mostly used lexicon-based methods [32, 33] or simple polarity classification [34], which fail to capture nuanced emotional states. No studies have yet applied advanced NLP architectures to journal data. This is furthermore hindered by data scarcity. Available datasets are small, predominantly in English, and lack continuous well-being labels or multimodal entries [35, 36]. German-language data are not publicly available. However, transfer learning offers a way to address these limitations by fine-tuning pre-trained models on small, domain-specific datasets [37, 38].

Input modalities are of further concern, as digital journal entries may be spoken or typed nowadays. This may influence the linguistics, as well as the model performance, as written text is more deliberate and structured [39], while spoken language contains paralinguistic cues such as prosody and pitch that can enhance emotion recognition [40, 41]. A previous study suggests that written text and transcribed speech may yield different prediction accuracies [42], but substantial research on the effect of the input modality on model performance is missing; especially in the context of emotional expression, such as in journaling.

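### Section 4.2.2 sets fine-tuned against frozen models only across different encoder sizes, and states no interval for differences between architectures

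*Protocol article*

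**What the plan says.** Section 4.2.2 (RQ1: NLP analysis) declares the aim: "The comparison of architecture classes is itself part of the study, as prior literature has not yet established a best-performing architecture for journaling data".

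It then describes two routes.

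- **Main route.** Sparse TF–IDF features and dense features are computed first. The dense ones are "contextual embeddings from German pre-trained transformer-based models like GBERT" or German-BERT. Learners from random forest and support vector regression to a BERT-based regression head are then fitted: "Separate predictive models will be trained on the above-mentioned representations for each outcome variable (MDBF subscales, PSS-4".
- **Additional route.** "We will additionally evaluate end-to-end fine-tuning of a smaller transformer model (e.g., a distilled German BERT variant". This model is one "which will operate directly on tokenized journal entries rather than precomputed representations". The article adds: "Here, we acknowledge the higher risk of overfitting compared to our main representation-based approach".

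All models are scored by RMSE, MAE and Pearson correlation in participant-level cross-validation, separately in the typed and transcribed groups. The text then says "Predictive performance metrics will then be compared across groups", and the next sentence provides for bootstrapped intervals on performance differences without naming the contrast.

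Section 4.2.6 (RQ5) takes the single best model forward to the comparison with experts. The intervals there concern model versus expert.

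**The concern.** The Introduction gives fine-tuning as a remedy for scarce data: "transfer learning offers a way to address these limitations by fine-tuning pre-trained models on small, domain-specific datasets". Section 4.1 takes its target of 500 entries per group from transfer-learning literature. A reader of the results will want to know whether fine-tuning helped at this sample size. As described, the fine-tuned model differs from the frozen ones in two respects at once: whether the encoder weights are trained, and how large the encoder is. If it does worse, overfitting (the risk that the article names in advance) and a weaker encoder are both possible explanations, and the planned runs do not separate them.

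The second part is uncertainty. An architecture comparison that is declared part of the study would be read from point estimates, although all architectures are scored on the same participants and entries and paired intervals are easily had. At stake is what the study may conclude about this aim. The hypothesis on typed versus spoken entries is not touched.

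**Working it through.** **1. Scale of the data (Section 4.1).** N = D / (d × (1 − r)) = 500 / (14 × 0.72) = 500 / 10.08 = 49.6, rounded up to 50 per group. This reproduces the plan. Fifty participants give 50 × 10.08 = 504 expected entries. Nothing here changes that figure.

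**2. What each contrast changes (Section 4.2.2).**

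| Contrast | What differs | Attributable? |
|---|---|---|
| Random forest, SVR, regression head on one representation | learner | yes |
| TF–IDF versus embeddings, learner fixed | representation | yes |
| Fine-tuned small model versus frozen GBERT or German-BERT features | training regime and encoder size | no |
| Fine-tuned versus frozen, same small checkpoint | training regime | yes, but not described |

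**3. Chance gaps between equal architectures.** The documents give no error correlation, clustering or number of models, so these are assumptions. One group has 50 participants × 10 entries = 500 entries. The error of model m is 0.9 × (√ρ × shared part + √(1 − ρ) × own part), with normal errors, each part clustered by participant. All models have the same true RMSE. The correlation ρ between models' errors is 0.7 to 0.95 and the participant ICC is 0.2 to 0.4, with 1,000 replicates per setting.

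| Models | Mean best-to-worst gap, % of RMSE | 95th percentile |
|---|---|---|
| 3 | 2.0 to 5.9 | 4.0 to 11.5 |
| 5 | 2.7 to 8.1 | 4.3 to 13.3 |
| 8 | 3.3 to 9.8 | 5.0 to 14.7 |

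The half-width of a paired 95% interval for two equal models is 1.96 × SD(D) / √50 / (2 × 0.9), divided by 0.9 to express it relative to RMSE. D is a participant's difference in mean squared error. This gives 3.2% to 9.7% of RMSE.

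**4. Wrong ranking of two models** (ICC 0.3, 4,000 replicates). Share of runs in which the truly worse model comes first:

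| True deficit in RMSE | ρ = 0.7 | ρ = 0.9 | ρ = 0.95 |
|---|---|---|---|
| 2% | 31.8% | 22.6% | 14.7% |
| 5% | 13.8% | 3.4% | 0.4% |

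**5. A second simulation, on the correlation scale.** Assumptions: six pipelines of equal true r = 0.4, 36 to 50 participants × 14 entries, outcome ICC 0.4, error correlation 0.5 to 0.85. The mean best-to-worst gap is 0.05 to 0.11 in Pearson r (2.6% to 5.4% of RMSE). The SE of the difference in r between two pipelines is 0.031 to 0.065 in one group and 0.021 to 0.045 with both groups combined. The ratios, 0.031 / 0.021 = 1.5 and 0.065 / 0.045 = 1.4, are about the √2 expected from doubling the data. The lower case (36 × 14 = 504 entries) matches the planned yield; the upper case (50 × 14 = 700) ignores the planned 28% loss.

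**The case against.** A reader might infer that no difference between architectures can be attributed. The table in step 2 shows otherwise: the main, representation-based comparison is sound, and only the arm labelled additional is affected.

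The other side also has these points.

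- **No hypothesis isolates fine-tuning.** Section 2 asks whether well-being and stress can be predicted, and whether spoken entries do better. This stands, and it limits the weight of the point. It does not remove it, because Section 4.2.2 itself makes the comparison of architectures part of the study.
- **The encoders are only examples.** A frozen run on the small checkpoint is not excluded, so the confounding cannot be called complete or fixed. But the restriction of fine-tuning to a smaller model is stated outright, and no matched run is described.
- **The interval sentence names no contrast, and details may sit in a plan not shown.** It could be extended to architectures. It does, however, close a run of sentences about group differences, which is its natural reading. If architectures were meant, one clause settles it.
- **The approach is exploratory (Section 3.1).** That supports a descriptive label for the ranking. It does not support an unqualified claim that one architecture is best.
- **RQ5.** A reader might infer that a chance winner damages the expert comparison. If the models are truly equal, carrying any one of them forward costs nothing. RQ5 is exploratory, and the expert-rated entries are left out of retraining.
- **The gap measure.** Best-to-worst gaps overstate the doubt about the winner, for which the runner-up matters. The two-model figures in step 4 are the more relevant ones.

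**Conclusion.** The point holds in a limited form. As described, the contrast of fine-tuned with frozen models mixes training regime with encoder size and cannot support a statement about fine-tuning. In context, no interval is stated for differences between architectures, so a best one would be named from point estimates.

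The size of the chance component is a few percent of RMSE: 2.0% to 9.8% on average from best to worst for three to eight equal models, and a 15% to 32% chance that a model truly 2% worse than its single rival is ranked first. These figures rest on assumed ICC, error correlation and number of models. Large true differences would be ranked correctly. The simulations bear on the ranking only and say nothing about how much encoder size matters.

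The documents do not support the stronger readings that the architecture comparison as a whole is uninterpretable, that the protocol plans intervals nowhere else (RQ5 has them), or that RQ5 is invalidated. This is an inexpensive improvement to what can be concluded about a declared aim.

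**What to change.** In Section 4.2.2:

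1. Also run the frozen-feature models on embeddings from the same checkpoint that is fine-tuned, with the same folds. Base any statement about fine-tuning on that matched pair.
2. Extend the bootstrap to paired differences between architectures for each outcome: same participants, same folds, participants resampled, group as stratum. The models stay trained within group, and the within-group differences are combined. Claim superiority only where the interval excludes zero, and otherwise report the ranking as descriptive.

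In Section 4.2.6, RQ5 may still take the model with the best point estimate. Say that this is a selection and not evidence that the model is superior, so that a tie in step 2 does not leave RQ5 without a model.

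The cost is one extra feature-extraction run and some analysis code, with no new data. The downside is that fewer architectures will be declared best.

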## Introduction

1

University students in Germany experience high levels of emotional distress, with 37% reporting emotional exhaustion [1]. Emotional exhaustion is a key risk factor for mental disorders and contributes to high dropout rates in higher education [2]. Stress plays a major role in deteriorating well-being [3], increasing the risk of mental health disorders [4], and impairing academic performance [5]. Additional factors such as poor physical health, sleep problems, anxiety, and loneliness further aggravate vulnerability [1]. Despite available interventions, such as Cognitive Behavioral Therapy (CBT) [6] and mindfulness practices [7], many students lack awareness and effective coping strategies [8, 9].

Journaling represents a low-cost, accessible, and increasingly popular practice among students, with social media trends further enhancing its appeal. Empirical evidence indicates that journaling can reduce anxiety and depression [10, 11], increase resilience [12], and foster acceptance of negative emotions [13]. For students, journaling has shown benefits in reducing stress [14], improving motivation [15], and enhancing academic performance [16]. However, effects vary depending on journaling type, duration, and population [17]. Journaling can also serve as a tool for monitoring emotional well-being. Traditional self-report instruments capture only limited aspects of subjective experience, while journaling allows for a richer and more ecologically valid picture of daily emotions and stressors [18]. This makes digital journaling particularly suitable for longitudinal monitoring in naturalistic settings. Compared to social media data, which has increasingly been used for mental health prediction [19], journaling allows for greater control over timing and context, as well as structured linkage to daily self-reports, providing a ground truth that has been noted as a persistent challenge in social media-based approaches [20]. Additionally, journaling carries a dual role, serving both as a monitoring tool and as an intervention shown to contribute positively to mental health.

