### Design

3.1

The study is a two-week observational study with an exploratory approach that uses NLP to explore the applicability of NLP-based analyses of journal entries for monitoring students’ emotional well-being and giving individual feedback. For this purpose, we will analyze the usage of spoken vs. typed journal entries for identifying mood and stress and determine which types of feedback are favored. In more detail, the study will investigate which type of input modality performs better in predicting the students’ emotional well-being using self-labeled journaling entries as ground truth. An overview of the study design is shown in Figure 1; further procedural details are provided in Section 3.3.

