Overview of the demographics describing the study population.Explanation, evaluation, and interpretation of the baseline questionnaires. Since the WHO-5 and the SCS-K-D do not provide a direct interpretation of their scores, averages from the German population were provided for comparison.A heat map and a line chart visualizing the MDBF values over time; the former based on the original scale of the questionnaire and the latter centered on the individual mean. Person-mean centering will be applied to make the questionnaire scores more interpretable for participants, with 0 reflecting each participant’s average for a given dimension. Negative scores will indicate worse-than-average scores, while positive scores will indicate better-than-average scores.A line graph visualizing the PSS-4 score over time, centered on the individual mean.A pie chart visualizing the distribution of the mentioned topics.Four times a bar chart showing the valence values of the MDBF over time, while centered on the individual mean. Individual charts will be colored according to the occurrence of the four most-mentioned topics. If the topic is mentioned on a day, the bar will be colored orange; otherwise, it will be colored gray. This should allow identifying relations between valence and topics.Three word clouds: one over all journal entries, one with words from the days with positive MDBF valence scores centered on the individual’s average, and one from the negative days. This should allow insights into predominant topics for better and worse days. In a pre-processing step, stopwords will be removed using Natural Language Toolkit (NLTK) [59].All (transcribed) journal entries with date and time.The feedback will conclude with a list of contact addresses for support services and assistance, and participants will be reminded that they may contact the study team at any time with questions regarding the feedback. In addition, participants whose DASS-21 scores exceed the respective cutoff values and who meet the age eligibility criteria will receive information about an additional study that offers access to psychological counseling.It should be noted that the feedback is based solely on each participant’s self-report data and does not incorporate any insights derived from the NLP analyses. This approach ensures that participants receive feedback that is independent of AI and remains accurate and meaningful even if model performance is suboptimal. The goal is to evaluate the capability of NLP models to infer indicators of users’ mental health (mood and stress), such that future studies may incorporate automatically generated feedback that includes these assessments. Should participants have questions about the feedback or feel uncertain or distressed by any of the information provided, they will be able to contact the study team for clarification and support.

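### The RQ1 performance metrics mix between-person and within-person association, so they cannot show whether a model follows a student's day-to-day mood and stress

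*Protocol article*

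**What the plan says.** Section 4.2.2 (RQ1: NLP analysis) fixes the metric set. On error it says "Model performance will be quantified using root mean squared error (RMSE) and mean absolute error (MAE) to capture prediction error magnitude"; on association it adds "Pearson correlation to assess the strength of association between predicted and observed scores". The comparator is also stated: "As a baseline, a mean predictor will be implemented". On clustering it says "To account for repeated measures within participants, cross-validation will be conducted at the participant level", so that no participant's entries fall in both training and test data. Models are trained and evaluated separately for the typed and transcribed groups, and the metrics are then compared with bootstrapped confidence intervals. No within-person, per-participant or person-mean-centred measure is named.

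The purpose is set elsewhere. Section 3.1 (Design) says the study uses NLP to "explore the applicability of NLP-based analyses of journal entries for monitoring" students' emotional well-being. The Introduction says of journaling: "This makes digital journaling particularly suitable for longitudinal monitoring in naturalistic settings". Section 3.4.3 adapts the mood and stress scales to the whole past day so that each day's scores can be predicted from that day's entry. Section 3.5 (Individual feedback) says "Person-mean centering will be applied to make the questionnaire scores more interpretable for participants". This centring applies to the mood line chart, the stress line graph, the four valence-by-topic charts and the better-day and worse-day word clouds. A heat map of mood stays on the original scale.

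**The concern.** Each participant can contribute up to 14 entries. The spread of daily scores then has two sources: some students are habitually higher or lower than others, and each student moves around their own level. A correlation or error measure on raw scores credits a model for either.

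Participant-level cross-validation stops a model from recognising a person it was trained on. It does not stop the model from using stable features of style or topic that go with a low or high average level and carry over to unseen students. Such a model would rank students and miss the changes from one day to the next.

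Monitoring over time, and charts centred on the person's own mean, need the second kind of information. Section 2 makes RQ1, together with RQ2, the condition for exploring automatic feedback, so it matters which kind of performance the RQ1 figures represent.

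**Working it through.** **The plan's own figure.** Section 4.1 gives 500 data points per group, 14 days and 28% dropout: 500 / (14 × 0.72) = 49.6, rounded to 50 per group. This reproduces. It implies about 14 × 0.72 ≈ 10 entries per participant and 50 × 10.08 = 504 per group. The point below does not affect the sample size.

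**Inputs not in the document (assumptions).** ICC is the share of outcome variance that lies between persons. r_b is the correlation of predictions with outcomes at person level, and r_w the same for daily deviations. ICC_pred is the share of prediction variance that lies between persons.

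**Formula.** Overall r = r_b × √(ICC × ICC_pred) + r_w × √((1 − ICC) × (1 − ICC_pred)).

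**Case A: no daily tracking, predictions constant within a person** (r_w = 0, ICC_pred = 1). Overall r = r_b × √ICC, the largest value possible when r_w = 0. With r_b = 0.6:

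| ICC | 0.3 | 0.4 | 0.5 | 0.6 |
|---|---|---|---|---|
| Overall r | 0.33 | 0.38 | 0.42 | 0.46 |
| Within-person r | 0 | 0 | 0 | 0 |

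Simulation with 50 persons × 10 entries and 1,000 runs gave 0.325, 0.373, 0.416 and 0.461, with a within-person r of 0.00 throughout. Averaging r over five person-level folds (the article does not give k) changes little: 0.392 against 0.416 at ICC 0.5.

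**Case B: no daily tracking, predictions vary by day as noise** (r_w = 0). With r_b = 0.6 and ICC = 0.5:
- ICC_pred = 0.5: 0.6 × √(0.5 × 0.5) = 0.30
- ICC_pred = 0.3: 0.6 × √(0.5 × 0.3) = 0.23

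**Case C: can the overall figure tell two opposite models apart?** At ICC = 0.5:
- Ranks persons only (r_b = 0.5, ICC_pred = 1): 0.5 × √0.5 = 0.35. Simulated r 0.345, RMSE 0.943 of the mean predictor's.
- Tracks days only (r_w = 0.5, ICC_pred = 0): 0.5 × √0.5 = 0.35. Simulated r 0.356, RMSE 0.940 of the mean predictor's.

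The two models are almost equal on r and on RMSE. MAE agrees (ratios 0.943 and 0.940).

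**RMSE against the mean predictor.** For a well-scaled prediction, the RMSE reduction is 1 − √(1 − r²). Case A at ICC 0.5 gives 1 − √(1 − 0.18) ≈ 9%. Case B with r = 0.30 gives 1 − √(1 − 0.09) ≈ 5%. A model with no daily tracking can therefore also beat the planned baseline on error.

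**The case against.** The strongest reply is that the article does not fix as much as a critic might assume. A reader might infer that RQ1 is judged by a single pooled Pearson correlation. The text does not support that: it never says pooled, it names RMSE and MAE first, and it sets no correlation threshold. This stands, but it does not remove the point. Averaging over folds has the same property, and RMSE and MAE against a mean predictor mix the two sources in the same way.

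A reader might also infer that a model without daily tracking would lead to automated monitoring being recommended. Section 2 says only that future work should go on to explore automatic feedback if RQ1 and RQ2 both hold, and Section 3.1 calls the approach exploratory.

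The size is open to challenge too. The models predict from each day's text, so their predictions will vary by day, and the person-constant formula is a ceiling. The prompt asks for the day's high and low points and the scales cover the same day, which favours some daily tracking. Nothing in the article makes zero tracking likely. All of this stands, and the figures show what the metrics could conceal, not what is expected.

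Third, RQ1 asks whether levels can be predicted, and between-person accuracy is a legitimate part of that. The heat map uses raw scores, and centring is justified by ease of reading. This also stands, and it is why the planned metrics should be kept.

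Finally, it is tempting to say that the typed-versus-spoken comparison is distorted by how different the people in each arm are. The arms are randomised in blocks, so a difference in between-person spread would arise only by chance, and the comparison carries bootstrap intervals. The article does not support a claim of bias there.

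**Conclusion.** The point holds in a limited form. The metrics named in Section 4.2.2 can answer whether mood and stress levels are predictable in unseen students. They cannot show whether a model follows change within a student, which the monitoring aim and most of the planned feedback charts require. A model with no within-person correlation could show an overall r of at most 0.33 to 0.46 (r_b 0.6, ICC 0.3 to 0.6), and about 0.30 at ICC 0.5 if half of its prediction variance is daily noise. With a low ICC the room for this is smaller: 0.6 × √0.2 = 0.27 at ICC 0.2. All of these rest on assumed values of ICC, r_b and ICC_pred. Nothing in the plan is invalidated; this is an inexpensive improvement that lets the study answer its own question.

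**What to change.** Keep RMSE, MAE, the overall Pearson correlation and the mean predictor. For each outcome (three mood subscales and stress) and each group, add two correlations computed on the out-of-fold predictions:

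1. **Within-person:** predicted and observed scores each centred on that person's mean.
2. **Between-person:** person means of predicted against person means of observed scores.

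Give both bootstrap intervals that resample participants, with all of a participant's entries kept together. State in Section 4.2.2 that any claim about tracking daily change, and the step towards automated feedback, rests on the within-person figure, while the overall figure answers whether levels can be predicted.

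The cost is a few lines of code on predictions that will exist anyway, with no new data and no change in sample size. A participant with only one usable entry adds nothing to the within-person figure, and that figure may be lower than the headline.
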